### Adverse events

An adverse event is defined as “any untoward medical occurrence in a clinical trial subject” [22]. An adverse event may or may not have a causal relationship with the treatment in the study. All adverse events observed by the investigator or study practitioner (e.g., physicians), or reported by the subjects, are to be recorded in the medical record of the subject. If a pre-existing medical condition of the subject worsens, this is considered one type of adverse event. For example, if a patients’ diabetes, migraine headaches or gout worsens in time (e.g., increased in severity, frequency of duration) with the administration of the treatment, this indicates that the administration of the treatment may be associated with a significant worse outcome in the subject.

All adverse events observed by the investigator or study practitioner (e.g., physicians) or reported by the subject after randomization through the end of study will be reported by the investigator to the applicable electronic Case Report Form (eCRF) (e.g., Adverse Event Summary eCRF).

#### Adverse event attributes

Below are the attributes the investigator must assign to each adverse event:Adverse event diagnosis or syndrome(s), if known (if not known, signs or symptoms),Dates of onset and resolution,Severity (and/or toxicity per protocol)Assessment of relatedness to investigation treatment, andAction taken

#### Adverse event assessment

Below is a list of questions the investigators must assess. Each question is answered with either a “yes” or “no”:Is there a reasonable possibility that the event may have been caused by the study intervention?Is there a reasonable possibility that the event may be related to screening procedures?Is there a reasonable possibility that the event may have been caused by a study activity/procedure?

#### Adverse events and laboratory tests

Laboratory tests results will be reviewed thoroughly by the investigator to determine whether the change in abnormal values from the baseline values is clinically significant (based on clinician’s own judgment). After reviewing the changes, the investigator will determine whether an adverse event will be reported.Abnormal laboratory findings that are not clinically significantly different from baseline values will not be recorded as adverse eventsLaboratory findings that are clinically significant, that require treatments or adjustments from the current treatment will be recorded as adverse eventsClinically sequelae should also be recorded as the adverse event, where applicable

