### Hypotheses and objectives

#### Hypotheses

Warm needling acupuncture and medicinal cake-separated moxibustion (short as “acupuncture and moxibustion” in the following text) is noninferior to active control, in subjects with hypercholesterolemia, on° percent change of LDL-C° absolute change of LDL-C° percent change of HDL-C° percent change of TC° percent change of TG° rate of subject achieving LDL-C goal
Acupuncture and moxibustion is superior to active control, in subjects with hypercholesterolemia, on safety and tolerability° Adherence

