#### Secondary outcomes

The secondary outcomes consist of three aspects: efficacy, safety and adherence. The efficacy outcomes include, from the baseline to the end of the study (after 12-week intervention and after another 4-week follow-up), the absolute change in LDL-C, the percentage change in HDL-C, the percentage change in total cholesterol (TC), the percentage change in TG, and the rate of subjects achieving LDL-C goal (see Table 5 in Appendix 1) [21]. The safety outcomes will be assessed by the physical examination, vital signs (including sitting blood pressure (BP) and heart rate (HR), electrocardiogram (ECG) and subject incidence of adverse events, after 12-week intervention and after another 4-week follow-up. The adherence outcome will be examined by the adherence rate, calculated as:$$ \mathrm{Adherence}\ \mathrm{Rate}=\mathrm{Number}\ \mathrm{of}\ \mathrm{treatments}\ \mathrm{conducted}/\mathrm{Number}\ \mathrm{of}\ \mathrm{treatments}\ \mathrm{planned}. $$

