### Blinding

Due to the nature of the acupuncture and moxibustion interventions, neither participants nor care providers can be blinded to allocation and treatment stages, but are strongly inculcated not to disclose the allocation status of the participant at the follow-up assessments. The outcome assessment will be conducted by outcome assessors blind to the treatment allocation. In the stage of data analyses, an employee outside the research team will feed data into the computer in separate datasheets so that the data analysts can analyze the data without having access to information about the allocation.

To maintain the overall quality and legitimacy of the clinical trial, code breaks should occur only in exceptional circumstances when knowledge of the actual treatment is absolutely essential for further management of the patient. Investigators, including the outcome assessors and data analysts blind to treatment allocation, are encouraged to discuss with the medical advisor physicians if they believe that unblinding is necessary. The investigator is encouraged to maintain the blind as far as possible. The actual allocation must *not* be disclosed to the patient and/or other study personnel. There should not be any written or verbal disclosure of the code in any of the corresponding patient documents. The investigator must report all code breaks (with reason) as they occur on the corresponding Case Report Form page. Unblinding should not necessarily be a reason for study drug discontinuation.

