#### Safety summaries and adherence analysis

Safety summaries will include the subject incidence of AEs, summaries of laboratory parameters, vital signs, and ECGs.

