However, certain limitations still exist in this study. One is the absence of a placebo control group due to the limited study budgets. Because of this lack of comparison, it may not be able to determine whether the outcome observed is due to the therapeutic effect of acupuncture and moxibustion or its placebo effect, if acupuncture and moxibustion is proved to be inferior to simvastatin. Nevertheless, judgment from clinical experiences and relevant findings from previous studies can help in identifying and justifying the effect with clinical significance.

Another limitation is the absence of blinding in patients and health care providers due to the operation characteristics of acupuncture and moxibustion. With patients knowing their intervention assignments after randomization, there may be a potentially higher possibility of cross-over between and drop-off from these two arms; thus, the potential selection bias may occur. But detailed explanation can be given to patients on these two arms of interventions in order to inform potential effects and safety in both arms. This will help limiting the drop-off and cross-over rates. Moreover, with the intervention assignment revealed, the effect identified from the acupuncture and moxibustion group may not fully result from its therapeutic aspect but a psychological aspect. But the outcome measures examined in this study are all objective – based on the fasting lipid level; and in the analysis process intervention assignment is fully blinding to data assessors. Therefore, the information bias due to lack of blinding could be controlled to a considerable extent.

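### Superiority on safety and tolerability is hypothesised, but adverse-event incidence is gathered and judged by people who know the allocation, and the claim that all outcomes are objective holds only for lipids

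*Protocol article*

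**What the plan says.** - **Hypotheses**: "Acupuncture and moxibustion is superior to active control, in subjects with hypercholesterolemia, on safety and tolerability". The matching secondary objective is weaker, since it only sets out to evaluate safety and tolerability.
- **Secondary outcomes**: safety is assessed by physical examination, vital signs, ECG and "subject incidence of adverse events, after 12-week intervention and after another 4-week follow-up". Laboratory values are not in this list.
- **Safety summaries and adherence analysis**: "Safety summaries will include the subject incidence of AEs, summaries of laboratory parameters, vital signs, and ECGs". Laboratory values do appear here.
- **Adverse events**: "All adverse events observed by the investigator or study practitioner (e.g., physicians), or reported by the subjects, are to be recorded".
- **Adverse events and laboratory tests**: the investigator reviews results to "determine whether the change in abnormal values from the baseline values is clinically significant", on the clinician's own judgment, and then decides whether an event is reported.
- **Blinding**: "neither participants nor care providers can be blinded to allocation and treatment stages". The same section promises outcome assessors and data analysts who are blind to allocation.
- **Discussion**, limitations: because "the outcome measures examined in this study are all objective", resting on fasting lipids, and because those analysing the data are blinded, information bias from the open design is said to be largely under control.

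**The concern.** A superiority hypothesis on safety needs events to be ascertained alike in both arms. Here the people who report events and those who decide what counts as one know which treatment was given. They also work from a protocol whose Background describes statins as having frequent side effects and acupuncture and moxibustion as having fewer serious events. The same change in a liver enzyme or CK could be called an event in one arm and passed over in the other. Blinding the analysts does not help, because an event that was never recorded cannot be recovered at analysis.

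The Discussion treats the matter as settled by the objectivity of the outcomes, and that reasoning does not reach the safety outcomes. A favourable safety comparison could then be presented as a finding of the trial when part of it came from how events were collected.

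**Working it through.** **1. Who knows the allocation, and who records events.** Stratified and blocked randomization has the biostatistician give physicians each allocation by telephone. The simvastatin dosage text has the investigator judge whether a subject tolerates the drug, which cannot be done without knowing the arm. Blinding states that participants and care providers are not blinded. The adverse-event sections give the investigator or physician the recording of events, severity, relatedness, the laboratory decision and withdrawal. They do not mention a blinded assessor or blinded adjudication.

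That the investigator is unblinded is an inference, though a strong one. Blinding, and the reporting procedures for serious adverse events, also use blinding language for investigators.

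**2. The objectivity statement against the outcome list.** Secondary outcomes has three parts: efficacy, safety and adherence. The efficacy part consists of lipid measures. Event incidence and the adherence rate are not lipid measures, and event incidence depends on report and judgment. The statement in the Discussion therefore holds for the first part only.

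**3. The only sample size in the protocol.** It is for LDL-C, not safety. With difference 0.343, SD 0.7, two-sided alpha 0.05 (the printed significance level of 0.95 read as confidence) and power 0.80:

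n per group = 2 × [0.7 × (1.960 + 0.842) / 0.343]² = 65.4

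This agrees with the stated figure of about 65. Nothing in it concerns event rates. I use 65 per arm below only as the scale of the trial.

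**4. What a few reclassified subjects do.** Moving k subjects changes one arm's incidence by k/65: 5/65 = 7.7 points and 8/65 = 12.3 points. Uncorrected chi-squared p-values, starting from equal counts in the two arms (all counts are assumed):

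| Equal starting count per arm | 5 more in one arm | 8 more in one arm |
|---|---|---|
| 0 | 0.023 | 0.004 |
| 1 | 0.052 | 0.009 |
| 5 | 0.170 | 0.042 |
| 6 | 0.193 | 0.052 |
| 10 | 0.266 | 0.088 |

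Five subjects cross 0.05 only from zero events in each arm. Eight do so only from five or fewer per arm, and with a continuity correction 5 v 13 gives 0.075. A handful of reclassified subjects is therefore not enough in general.

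**5. What a systematic reporting difference does.** Assume equal true incidence p in both arms, full recording under simvastatin, and a fraction s of events recorded under acupuncture. The table gives the exact binomial probability, with 65 per arm, that an uncorrected chi-squared test at two-sided 0.05 falsely favours acupuncture:

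| p | s = 1.0 | s = 0.9 | s = 0.8 | s = 0.6 |
|---|---|---|---|---|
| 10% | 0.025 | 0.039 | 0.059 | 0.131 |
| 30% | 0.026 | 0.059 | 0.120 | 0.365 |
| 50% | 0.022 | 0.075 | 0.199 | 0.655 |

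The values of p and s are assumptions, since the protocol gives neither. The table shows sensitivity and does not forecast this trial.

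**The case against.** - **Event incidence is not the whole of safety.** Vital signs and ECG are safety outcomes, laboratory parameters are to be summarised, and all on-study samples go to the central laboratory. This stands. A reader might infer that the safety claim rests entirely on subjective reports, and the documents do not support that.
- **No confirmatory safety test is designated.** The objective is to evaluate, the analysis section offers summaries, and the primary-type analysis is extended only to other secondary efficacy endpoints. This also stands, although the general sentence on chi-squared tests for binary outcomes could be applied to event incidence. It makes the superiority wording in Hypotheses the part that is out of step.
- **Blinded assessors and analysts are planned.** They are, but the adverse-event sections do not give them this task.
- **Investigator judgment is ordinary practice, and the laboratory rule also mentions findings that require treatment or an adjustment of treatment.** That is fair for individual reporting and care. It does not make the two arms comparable when the clinician deciding knows the arm.
- **The objectivity sentence is about the treatment effect and claims only considerable control.** The context softens it, but the word *all* remains wrong.
- **Bias in favour of acupuncture.** A reader might infer this from the Background. It is plausible, but neither direction nor size can be shown from the documents.
- **Testing superiority on liver enzymes and CK alone.** This is a tempting remedy and it is unsound. It would judge safety only where statin harm is expected and would leave burns, needling events and tolerability untested.

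**Conclusion.** The point holds in a limited form. The protocol hypothesises superiority on safety and tolerability, while one main component of safety is ascertained by people who know the allocation, with no numeric rule for laboratory events and no stated role for the blinded assessors. The Discussion's reassurance applies to lipid outcomes only. A difference in event incidence could therefore be partly an artefact of ascertainment.

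The size is unknown. In the assumed scenarios, recording 80% of events in one arm raises the false-superiority probability from between 0.022 and 0.026 to between 0.059 and 0.199, whereas isolated reclassification of five subjects matters only when events are almost absent. The conclusion rests on reading the investigator who records events as unblinded, which the randomization and dosage text strongly suggests. It concerns a secondary hypothesis and does not touch the LDL-C endpoint. It is worth correcting because the correction is cheap and changes what the trial can claim about safety.

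**What to change.** 1. **Adverse events and laboratory tests; Secondary outcomes.** For the comparison between arms, have the allocation-blind analysts also count laboratory exceedances by fixed central-laboratory cut-offs applied identically to both arms. The multiples already in the exclusion criteria (AST or ALT above 2 × ULN, CK above 3 × ULN) are one example. They apply at initial screening or at the end of lipid stabilization, so a later exceedance would generally be new. List the count as a laboratory-safety outcome. Leave investigator judgment in place for individual reporting and care.
2. **Hypotheses.** Replace superiority on overall safety and tolerability with an evaluation that matches the secondary objective and the planned safety summaries. Report all adverse events descriptively by arm, including needling and burn events. Do not restrict a safety-superiority claim to AST, ALT and CK.
3. **Discussion.** Limit the objectivity statement to lipid outcomes, and acknowledge that adverse-event reporting is open to bias from the lack of blinding.

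The cost is wording in these sections and one derived variable from samples already sent to the central laboratory, whose panel includes AST, ALT and CK. The downside is that some counted exceedances will not be clinically important and the safety claim becomes narrower.

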#### Adverse events and participant withdrawal

The investigator will use his/her clinical judgment to determine whether a subject should be removed from the study due to adverse events. The subject or their legal representatives also have the full right to withdraw from the treatment due to an adverse event or concerns for an adverse events. However, the investigator will encourage the subjects to undergo at least an end of the study assessment.

### Serious adverse events

#### Definition

A serious adverse event is defined as an adverse event that meets at least one of the following criteria:FatalLife-threatening (places the subject at immediate risk of death)Requires in-patient hospitalization or prolongation of existing hospitalization, (the criterion of “requires hospitalization” for an adverse event, indicates an event necessitated an admission to a health care facility, e.g., overnight stay in hospital)Results in persistent or significant disability/incapacityCongenital anomaly/birth defectOther medically important serious event

A serious adverse event can still be recorded if an investigator considers an event to be clinically significant. In this case, the event will be classified as “other medically important serious event” and comprehensive documentation of the events’ severity will be recorded on the subject’s medical record. Some examples of this include: allergic bronchospasm, convulsions, blood dyscrasia, or events that necessitate an emergency room visit, outpatient surgery, or urgent intervention.

#### Reporting procedures for serious adverse events

All observed or reported serious adverse events after randomization through 4 weeks after the last investigational treatment will be recorded on the subjects’ medical records by the investigator and submitted to the principal investigator within one working day of discovery of the adverse event. These include: new information reported on a previously known serious adverse event, serious adverse event possibly related to the treatment, and full withdraw by the subject from the study due to serious adverse event.

In the case of a serious, unexpected, and related adverse event, the subject may be unblinded by the investigator prior to submission of the adverse event to the regulatory authority. Investigators will receive information on how to report adverse serious events to authorities in accordance to local requirements and Good Clinical Practice prior to the clinical trial. All serious adverse events will be reported to appropriate Independent Ethics Committee (IEC).

### Pregnancy reporting

If a pregnancy occurs during the time when the female subject is undertaking the study intervention, the pregnancy should be reported to the research team. Pregnancy after undertaking the study intervention for an additional 4 weeks should also be reported.

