### Exclusion criteria

Subjects are excluded from the study if they are diagnosed with one or more of the following conditions:Coronary heart disease (CHD) or CHD risk equivalent who are not receiving statin therapy with LDL-C at screening of ≤99 mg/dLHeart failure of New York Heart Failure Association (NYHA) class II, III or IV or last known left ventricular ejection fraction <30%Cardiac arrhythmia within 3 months prior to randomization that is not controlled by medicationMyocardial infarction, unstable angina, percutaneous coronary intervention (PCI), coronary artery bypass graft (CABG) or strokePlanned cardiac surgery or revascularizationType 1 diabetes;Newly diagnosed type 2 diabetes (within 6 months of randomization or new screening fasting plasma glucose ≥126 mg/dL (7.0 mmol/L) or HbA1c ≥6.5%), or poorly controlled type 2 diabetes (HbA1c >8.5%)Persistent systolic blood pressure (SBP) >160 mm Hg or diastolic BP (DBP) >100 mmHgThyroid stimulating hormone (TSH) < lower limit of normal (LLN) or TSH >1.5 × upper limit of normal (ULN), estimated glomerular filtration rate (eGFR) <30 ml/min/1.73 m^2^, aspartate aminotransferase (AST) or alanine aminotransferase (ALT) >2 × ULN, creatine kinase (CK) >3 × ULN (all at initial screening or at the end of lipid stabilization period(s) by the central laboratory)Known major active infection, or major hematologic, renal, metabolic, gastrointestinal or endocrine dysfunctionDeep vein thrombosis or pulmonary embolism within 3 months prior to randomization

Subjects are also excluded if they have taken any of the following medications for more than 2 weeks in the last 3 months prior to LDL-C screening: systemic cyclosporine, systemic steroids, isotretinoin (e.g., Accutane). Some anticoagulation treatments are also excluded (antiplatelet agents are permitted). Female subjects cannot be pregnant or be breastfeeding and premenopausal women must have to be willing to use at least one highly effective method of birth control during treatment and for an additional 15 weeks after the end of treatment.

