### Outcome measurements

#### Primary outcome

The primary outcome is the percentage change from baseline to the end of the study (after the 12-week intervention and after another 4-week follow-up) in LDL-C. The calculated LDL-C concentration will be determined at screening (entry to the study), day 1 (after TLC is completed and eligibility is determined), week 6, and week 12. LDL-C will be measured by preparative ultracentrifugation by the central laboratory. The LDL-C concentration calculated at screening will be reported only for the eligibility decision. The baseline lipid measurements for the purpose of analysis will be the day-1 lipid measurement after TLC (lipid stabilization). This will be collected after a ≥9-h fast and before receiving intervention.

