##### Week 12 end of study visit (±3 days)

Re-assessment on the study indicators of subjects will be conducted, including efficacy, safety, and adherence.

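### Contraception is required for 15 weeks after treatment but pregnancy reports are asked for only 4; secondarily, the stated SAE window closes before a congenital anomaly could be seen at birth

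*Protocol article*

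**What the plan says.** Five places in the protocol article bear on this.

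- **Exclusion criteria.** The condition for premenopausal women reads: "use at least one highly effective method of birth control during treatment and for an additional 15 weeks after the end of treatment".
- **Pregnancy reporting.** A pregnancy during the intervention goes to the research team. The section then adds: "Pregnancy after undertaking the study intervention for an additional 4 weeks should also be reported".
- **Serious adverse events, Definition.** A congenital anomaly or birth defect is one of the listed criteria for seriousness.
- **Reporting procedures for serious adverse events.** The instruction to record events and send them to the principal investigator covers "All observed or reported serious adverse events after randomization through 4 weeks after the last investigational treatment". Two further sentences in that section carry no time limit. One says that every SAE goes to the ethics committee. The other reads: "Investigators will receive information on how to report adverse serious events to authorities in accordance to local requirements and Good Clinical Practice".
- **Adverse events.** Entry in the electronic case report form runs from randomization to the end of the study. One heading calls week 12 the end ("Week 12 end of study visit"), while the Primary outcome section also counts the 4-week follow-up, which ends at week 16.

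**The concern.** A contraception period normally marks the time in which the trial regards conception as a possible risk from treatment. Pregnancy reporting is how the trial learns that the risk has occurred. Here the first period is nearly four times as long as the second, and nothing in the article explains the difference. Either pregnancies go unasked-for in a period that the protocol treats as one of risk, or an eligibility condition is longer than this trial needs.

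The second issue does not depend on the 15 weeks. The protocol names a congenital anomaly as an SAE, but its explicit window for recording and submitting SAEs ends before a birth could reveal one. Capture would then rest on sentences that give no timing.

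The stake is completeness of safety reporting for a very small number of women. Efficacy conclusions are not involved.

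**Working it through.** **Inputs from the article.** Treatment lasts 12 weeks and follow-up 4 weeks (Trial design). Contraception lasts 15 weeks after treatment (Exclusion criteria). Pregnancy reporting lasts 4 weeks after treatment (Pregnancy reporting). The SAE window lasts 4 weeks after the last treatment (Reporting procedures for serious adverse events). About 70 subjects per group are to be randomized, so 2 × 70 = 140 (Sample size).

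**Assumptions, not in the article.** Premenopausal women make up 10% to 40% of subjects. Contraceptive failures run at 1 to 6 per 100 woman-years. Birth comes 22 to 38 weeks after conception.

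The article gives no figure of its own to reproduce on this point.

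**Step 1: contraception against pregnancy reporting, in weeks from day 1.**
- Contraception ends at 12 + 15 = week 27.
- Pregnancy reporting ends at 12 + 4 = week 16.
- Gap if 15 weeks is intended: 27 − 16 = 11 weeks, and 11/15 = 73% of the post-treatment contraception period.
- Gap if the Exclusion criteria should have said 4 weeks: 16 − 16 = 0.

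Both periods count from the end of treatment, so stopping treatment early leaves the 11 weeks unchanged.

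**Step 2: SAE window against birth.** The window closes at week 16 at the latest. It closes earlier for a woman who stops treatment because she is pregnant, which is a listed reason for discontinuing.
- Conception on day 1: birth falls 22 − 16 = 6 to 38 − 16 = 22 weeks after the window closes.
- Conception at week 16, the last that the article asks to be reported: birth falls 16 + 22 − 16 = 22 to 16 + 38 − 16 = 38 weeks after it closes.
- With a term range of 35 to 40 weeks instead, a day-1 conception gives birth 35 − 16 = 19 to 40 − 16 = 24 weeks after it closes.

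No value in either range brings such a birth inside the window. The case-report-form rule, ending at week 12 or week 16, does not reach it either.

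**Step 3: how many pregnancies.** Expected number = women × failure rate × weeks/52. The number of women is 140 × 0.10 = 14 to 140 × 0.40 = 56.
- Weeks 16 to 27 (the gap): 14 × 0.01 × 11/52 = 0.03 to 56 × 0.06 × 11/52 = 0.71.
- Weeks 0 to 16 (already reportable): 14 × 0.01 × 16/52 = 0.04 to 56 × 0.06 × 16/52 = 1.03.
- Both together: 0.03 + 0.04 = 0.07 to 0.71 + 1.03 = 1.74.

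The upper figures need the top of both assumed ranges at once.

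**The case against.** The strongest reply has three parts.

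**The two periods do not conflict.** A contraception rule and a reporting rule are different instructions, and a site can follow both. A reader might infer that the protocol contradicts itself; it does not. What stands is a mismatch that the article leaves unexplained.

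**The 15 weeks may not belong to this trial.** Appendix 2 contains material foreign to it: antibodies to AMG 145 in the laboratory table, an exclusion numbered 4.2.17, and a reference to a parent study. Pregnancy reporting, SAE recording and the last visit all stop 4 weeks after treatment, so the 15 is the odd number out. A reader might therefore take the 11-week gap as established, or take the carry-over as proven. The article settles neither. In either case one number needs attention.

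**Following pregnancies to outcome is something a condensed article may leave out.** This is fair. A reader might infer that the trial has no such follow-up or that birth defects would go unreported. The article does not support that: the full protocol is not shown, and the ethics-committee and Good Clinical Practice sentences may well prompt a late report. What stands is narrower. The article itself states a time limit for SAEs, and neither of those sentences makes an exception to it. The wording on new information about a known SAE does not help, because an uneventful pregnancy is not an SAE under the listed criteria.

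An anomaly could also be found before birth and inside the window. The secondary point concerns only one first seen at birth.

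**Conclusion.** The point holds as a minor safety-reporting mismatch. If the 15 weeks is intended, 11 post-treatment weeks of required contraception have no request for a pregnancy report. If it is a carry-over, the gap is zero and the fault is an unneeded condition on premenopausal women in the Exclusion criteria. The week counts come straight from the article; which branch applies is for the sponsor to say.

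The secondary point holds on the stated SAE window alone, subject to anything in the full protocol. It depends on an assumed time from conception to birth, but no value in the ranges used changes the result. It is limited to conceptions on or after day 1, since pregnant women are excluded.

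The expected number of pregnancies is about one at most in either period. That rests on the assumed share of premenopausal women and the assumed failure rate, neither of which the article gives. The primary endpoint, sample size and analyses are unaffected. The change is worth making because it is nearly free.

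**What to change.** 1. Make the two periods equal. By default, extend the Pregnancy reporting section from 4 to 15 weeks after treatment. If the sponsor confirms that 15 weeks does not belong to this trial, correct the Exclusion criteria instead.
2. Unless the full protocol already says so, add one sentence to Reporting procedures for serious adverse events: a congenital anomaly from any reported pregnancy is reported as an SAE whenever it is discovered.

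**Cost.** Two wording changes and follow-up of any reported pregnancy to its outcome: about one at most with reporting to week 16, and fewer than two in total if it is extended to week 27, on the assumptions above. Keeping 15 weeks also means one phone call to premenopausal women at week 27, which is 11 weeks after the last scheduled visit.
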